#### Secondary endpoints

Secondary endpoints that will be assessed include health-related QOL, as measured by the ‘Modified Roseblatt Index,’ [16] major complications and treatment-related mortality. The ‘Modified Rosenblatt Index’ is a questionnaire assessing patient-reported outcomes previously developed for use among EC patients by Rosenblatt, et al., which has been adapted for use within a resource-limited context (see Table 2) [16]. Parameters evaluated as part of this index are scored on a Likert scale assessing the presence and severity of the following: Dysphagia, Odynophagia, ‘Chest and/or Back pain,’ World Health Organization (WHO) performance status, and ‘Overall Well-being’ since starting treatment. Secondary outcome measures related to dysphagia will also be assessed as dysphagia is commonly a dominant symptom among patients with advanced disease. These secondary measurements include time to achieve any dysphagia relief, time to achieve maximal dysphagia relief, duration of dysphagia relief, and dysphagia-adjusted survival.

**Table 2 Tab2:** Quality of life metrics as measured by ‘Modified Rosenblatt Index’^a^

	Score				
	0	1	2	3	4
**Dysphagia** Which of the following best describes your ability to swallow?	Normal	Can swallow most foods	Can swallow a soft diet	Can swallow fluids only	Unable to swallow saliva
**Odynophagia** Which of the following best describes the severity of pain you experience when swallowing?	No pain	Mild pain	Moderate pain	Severe pain	–
**Regurgitation** Which of the following best describes how frequently you experience acid reflux, heart burn and/or the sensation of burning in the esophagus?	Never	Infrequent	Frequent	Constant	–
**Chest-back pain** Which of the following best describes your chest and/or back pain?	No pain	Pain relieved by non-narcotics	Pain not relieved by non-narcotics or requiring an opiate medication	–	–
**WHO Performance status** Which of the following best describes your symptoms and activity level on a daily basis?	Fully active, able to carry on all pre-disease performance without restriction	Restricted in physically strenuous activity but ambulatory and able to carry out work of a light or sedentary nature	Ambulatory and capable of all selfcare but unable to carry out any work activities. Up and about more than 50% of waking hours	Capable of only limited selfcare, confined to bed or chair > 50% of waking hours	Completely disabled. Cannot carry on any selfcare. Totally confined to bed or chair
**Overall well-being** Which of the following best describes your quality of life now as compared to before you were treated for esophageal cancer?	“A lot better”	“A little better”	“The same”	“A little worse”	“A lot worse”

^a^Modified quality of life index reprinted with permission from Rosenblatt (2010, Table 1)

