### Study design

This study is designed as a multi-center, prospective, observational, open cohort study. Initiation of recruitment has been staggered across sites, with the earliest commencing in February 2019 and additional sites beginning recruitment in 2021. Enrollment is scheduled to complete in December 2022, with follow-up to complete in June 2023. In total, approximately 2476 patients are expected to be enrolled in the study. Patients will be followed to collect key clinical and treatment-related data including overall survival and QOL metrics until death or loss to follow up. QOL metrics will be assessed at the time of study enrollment, prior to the initiation of treatment, and during post-treatment follow up (1 month after initiation of treatment, 3 months after initiation of treatment, and then every 3 months until death or loss to follow up). The accrual period is expected to range between 22 and 47 months across sites. Duration of follow up will differ by site due to the staggered initiation of recruitment, however, study participants will be followed for at least 6 months and up to a total of 53 months.

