### Eligibility criteria

Patients aged ≥18 years with a diagnosis of EC will be eligible for study inclusion. Expanded inclusion criteria will be used as not all patients with suspected EC undergo diagnostic biopsies due to the costs associated with biopsy and pathological review. Diagnostic criteria for EC will include either histopathological confirmation or clinical diagnosis based on barium swallow (esophagram) and/or upper endoscopy without biopsy. This clinical criteria has been shown to have a > 90% pre-test probability for the diagnosis of ESCC in Eastern Africa [17]. Access to a mobile phone is not a requirement for study entry; however, should a study participant lack access, this will be noted on baseline enrollment forms. Patients who have previously received treatment for EC will be eligible for study participation; in these cases, details of prior EC treatment will be abstracted from medical records, if available.

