### Data collection procedures

#### Case report forms (CRFs)

CRFs are comprised of both medical chart abstraction instruments and standardized questionnaires. CRFs collect socio-demographic details (including age, sex, ethnicity, location of permanent residence, highest level of education completed, self-reported annual household income, health insurance status), baseline clinical information, treatment-related data, as well as vital status and QOL metrics over long-term follow up (see Table 3).

**Table 3 Tab3:** Data collected during TOEC-Eastern Africa study

Collected data	Baseline	Prior to treatment	During treatment	Follow up^**a**^
Sociodemographic				
Age	x			
Sex	x			
Ethnicity	x			
Occupation	x			
Location of permanent residence	x			
Highest level of education completed	x			
Annual household income	x			
Health insurance status	x			
Smoking and alcohol use	x			
Clinical data				
Medical History	x			
HIV status (date of and last CD4 count, use of antiretrovirals)	x			
Date/method of diagnosis	x			
Histopathological data (if applicable)	x			
Endoscopic findings (location/length of tumor)	x			
Imaging (if applicable)^b^	x			
Use of opiate medications for pain control	x	x		x
Hospitalizations			x	x
Vital status (including cause of death, if applicable)			x	x
Treatment				
Prior EC treatment (if applicable)	x			
EC treatment received, including delays/interruptions in treatment and reasons			x	
Complications			x	
Response assessment (if applicable)			x	
Quality of life				
Modified Rosenblatt Index^c^	x	x		x

*EC* Esophageal cancer

^a^Follow up assessments performed 1 month after initiation of treatment, 3 months after initiation of treatment, and then every 3 months until death or loss to follow up

^b^Any imaging modality performed during baseline assessment, including chest x-ray, ultrasound, computed tomography, positron emissions tomography, etc.

^c^The Modified Rosenblatt Index assesses the following: Dysphagia, Odynophagia, ‘Chest and/or Back pain,’ WHO performance status, and ‘Overall Well-being’ since starting treatment

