#### Patient interviews

Interviews with study participants will be conducted at the following specified time-points: (i) at time of study enrollment); (ii) prior to the initiation of treatment (within 4 weeks); and (iii) during post-treatment follow up (1 month after initiation of treatment, 3 months after initiation of treatment, and then every 3 months until death or loss to follow up). Research assistants will collect data on sociodemographic characteristics, medical history, and baseline QOL through face-to-face administration of oral questionnaires at the time of study enrollment. QOL assessments are based on the ‘Modified Rosenblatt Index,’ [16] a questionnaire comprised of six patient-reported outcomes assessing for the presence and severity of the following as scored on a Likert scale: Odynophagia, Dysphagia, ‘Chest and/or Back pain,’ WHO performance status, and ‘Overall Well-being’ since starting treatment (see Table 2). Subsequent interviews assessing vital status and QOL will be performed through mobile phone outreach. During post-treatment follow up, research assistants will attempt to contact patients a minimum of three times over the follow up interval before patients are classified as “lost to follow up.” Outreach attempts will be made at varying times of the day on three different days of the week.

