Cochran-Armitage test will be used to compare symptom metrics assessed using the ‘Modified Rosenblatt Index’ (Dysphagia, Odynophagia, ‘Chest and/or Back pain,’ WHO performance status, and ‘Overall Well-being’ since starting treatment) between each of the different palliative EC treatments (chemotherapy, radiotherapy, chemoradiation, esophageal stenting, basic supportive care) at each time point: 1 month after initiation of treatment, 3 months after the initiation of treatment and then every 3 months thereafter. We will also test for within-subject differences in scores between baseline (or pre-treatment) and each of post-treatment time points by McNemar’s Chi-squared test. In addition, generalized estimating equations (GEE) framework will be applied to analyze this longitudinal QOL data, where the treatment will be considered as the fixed effect and the subject-specific effects are the random effects.

Complications will be summarized as number of patients (%) with 95% confidence intervals and compared between treatment arms by Chi-squared test. Among palliative interventions, secondary outcome measures related to dysphagia will be compared using log-rank test and cph models to adjust covariates, including age, sex and baseline clinical covariates. ‘Time to achieve any dysphagia relief’ will be defined as time from treatment to improvement in dysphagia score of greater than or equal to 1. ‘Duration of dysphagia relief’ will be defined as time elapsed after treatment with any improvement in dysphagia from baseline. ‘Dysphagia-adjusted survival’ will be defined as the total time period with a dysphagia score of 0 to 2.

Measures of healthcare utilization and process measures related to the delivery of ESCC treatment by treatment approach will be examined as exploratory endpoints. Time-to-event measures will be compared among treatment groups by log-rank test. Count of hospitalization events, and total number of days hospitalized during and after ESCC treatment will be compared among treatment groups by ANOVA (or Kruskal Wallis test when normality assumption is not held). Chi-squared test will be used to compare the need for subsequent intervention for recurrent or persistent dysphagia by treatment approach. All analyses will be performed overall and within each site.

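### The Overall well-being item rates change since before treatment, so the planned within-subject test of it against a pre-treatment score cannot be interpreted, and its anchor is undefined for supportive care

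*Protocol article*

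**What the plan says.** Table 2 (Secondary endpoints) asks, for Overall well-being: "Which of the following best describes your quality of life now as compared to before you were treated for esophageal cancer". Answers run from 0 ('a lot better') through 2 ('the same') to 4 ('a lot worse'). The other five items in Table 2 ask about present symptoms or activity. The Patient interviews section gives the item the same reference period: "WHO performance status, and ‘Overall Well-being’ since starting treatment (see Table 2".

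On timing, Study design states: "QOL metrics will be assessed at the time of study enrollment, prior to the initiation of treatment, and during post-treatment follow up". Patient interviews adds that research assistants collect "baseline QOL through face-to-face administration of oral questionnaires at the time of study enrollment". Table 3 marks the index at baseline, prior to treatment and at follow-up. Its footnote c begins "The Modified Rosenblatt Index assesses the following: Dysphagia, Odynophagia" and goes on to include Overall Well-being, with no exception for the two pre-treatment columns.

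On analysis, Statistical methods names Overall Well-being among the metrics compared between five groups, one of them basic supportive care, at 1 month, 3 months and every 3 months after treatment starts. It continues: "We will also test for within-subject differences in scores between baseline (or pre-treatment) and each of post-treatment time points". The named method is McNemar's test. A GEE analysis of the longitudinal QOL data follows. Neither sentence sets this item apart.

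Eligibility criteria also states: "Patients who have previously received treatment for EC will be eligible for study participation".

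**The concern.** A question that already asks about change cannot supply its own baseline. Asked before any treatment, it leaves a treatment-naive patient to guess: skip it, say 'the same', or compare with life before the illness. A previously treated patient can answer, but about a different treatment. Pairing either answer with a follow-up rating that is itself a change gives a change of a change, from a mixture of reference points.

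The supportive-care comparison raises a related difficulty. The question refers to the time before treatment, and the article does not say what date that is for a patient who receives supportive care alone.

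This is the only global quality-of-life rating in the index. The Discussion presents QOL by treatment as a first for sub-Saharan Africa and as possible input to practice guidelines. An apparent within-patient gain or loss on this item could be cited although it reflects only how the baseline question was read.

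**Working it through.** **The plan's own figures.** The article gives no power or effect size for this item, so there is none to reproduce. The relevant figures are the expected group sizes under Sample size: 1102 + 145 + 464 + 212 + 450 + 103 = 2476, which matches the stated total. Supportive care alone is 450/2476 = 18.2% of the cohort, or 450/(2476 - 103) = 450/2373 = 19.0% once esophagectomy is left out. Among the five groups compared on QOL there are 5 × 4/2 = 10 possible pairs, and supportive care is in 4 of them.

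**Tracing the item through the plan.**

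| Step | Place | Consequence for this item |
|---|---|---|
| Wording | Table 2 | Change against the time before treatment |
| Schedule | Study design, Patient interviews, Table 3 | Asked at enrollment and before treatment, with no exemption |
| Within-subject test | Statistical methods | Baseline or pre-treatment paired with follow-up, with no exemption |
| Between-group test | Statistical methods | Post-treatment times only, five groups including supportive care |

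The second and third steps conflict with the first. The fourth conflicts only where supportive care is one of the groups.

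**How far the within-subject result can move.** The article says nothing about how patients answer before treatment, so the distributions below are assumptions for illustration. Follow-up answers are held fixed, with proportions 0.30, 0.30, 0.20, 0.10, 0.10 on scores 0 to 4:

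- Follow-up mean = 0.30×1 + 0.20×2 + 0.10×3 + 0.10×4 = 1.40, which is 1.40 - 2 = -0.60 against 'the same'.
- Proportion better (score 0 or 1) = 0.30 + 0.30 = 0.60.

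Three ways of answering at baseline:

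- A: everyone says 'the same'. Mean 2.00, proportion better 0.
- B: compared with life before the illness, proportions 0.02, 0.05, 0.13, 0.30, 0.50. Mean = 0.05 + 0.26 + 0.90 + 2.00 = 3.21, proportion better 0.07.
- C: benefit from an earlier treatment, proportions 0.40, 0.30, 0.20, 0.05, 0.05. Mean = 0.30 + 0.40 + 0.15 + 0.20 = 1.05, proportion better 0.70.

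McNemar's test compares paired proportions and computes no point difference. The last column therefore splits the scale at better versus not better, a cut assumed here, and gives the net shift that the test assesses (follow-up minus baseline proportion better).

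| Baseline reading | Mean change (negative = better) | Net shift to better |
|---|---|---|
| A | 1.40 - 2.00 = -0.60 | 0.60 - 0 = +0.60 |
| B | 1.40 - 3.21 = -1.81 | 0.60 - 0.07 = +0.53 |
| C | 1.40 - 1.05 = +0.35 | 0.60 - 0.70 = -0.10 |

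The follow-up answers are identical in all three rows. The contrast changes size and, in row C, sign, solely because of the baseline reading. Measured directly against 'the same', the result is -0.60 in every row, with 60% better and 20% worse.

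**The case against.** The strongest reply is that the authors plainly know this is a post-treatment item, since they label it as running from the start of treatment, and that the case report form may skip it beforehand. Table 3 gives one row to the whole index, and the McNemar sentence speaks of scores without naming this item. What stands is that the form is not shown, so nobody can say from the article that the question was put to patients before treatment. But no skip is stated anywhere. Table 3 marks other rows as applying only where applicable and does not do so here, and the same paragraph that names Overall Well-being goes on to the within-subject test without exempting it. Followed as written, the plan pairs the answers.

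Two further replies are right and limit the point. Study objectives and Statistical methods count supportive care among the palliative interventions, so that group's anchor is undefined rather than absent. And the between-group comparison is made only after treatment starts, so among actively treated patients a rating of change remains interpretable.

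A reader might also infer that the plan will make treatments look beneficial by as much as 2 points, because an unchanged patient could move from 'a lot worse' before treatment to 'the same' afterwards. The documents do not support that. They do not say how patients answer at baseline, previously treated patients may answer 0 or 1 and then appear to worsen, and McNemar's test forms no point difference.

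**Conclusion.** The point holds for one item and two uses of it. The within-subject test of Overall well-being against a baseline or pre-treatment score is uninterpretable, and its error can go either way. Its size cannot be stated from the article; the three figures in the illustration rest on assumed answers and show only that size and sign depend on the baseline reading. The comparison with basic supportive care, 18.2% of expected patients, lacks a defined anchor.

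It would be too strong to conclude that every result on this item is without meaning, or that the QOL endpoint fails. Post-treatment comparisons among actively treated groups stand, the other five items ask about current state, and the primary overall survival analysis is untouched. The conclusion assumes that the article's schedule and analysis are carried out as printed. It should be corrected, but it does not threaten the main result.

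**What to change.** - Collect Overall well-being only after treatment starts, or, where it is already asked earlier, set the pre-treatment answers aside. Mark this in Table 3.
- Remove the item from the McNemar test and from any other analysis of change from baseline, including the GEE model if pre-treatment scores enter it.
- Test follow-up ratings directly against 'the same' (score 2), for example with a sign or signed-rank test, since each rating already expresses the change.
- Limit the between-group comparison on this item to the actively treated groups.

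No re-wording of the question is needed. With recruitment running since February 2019 and staggered across six sites, a new wording would mix two versions of the item.

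The work is a clarification of the form schedule and the analysis text, with one question fewer at two time points. The loss is the supportive-care comparison on this one item; supportive care can still be compared on the other items.

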#### Exploratory endpoints

Exploratory endpoints related to processes of care will also be measured, including time from presentation to initiation of ESCC treatment, time to deliver intervention (defined as total time elapsed from initiation of treatment to last day of treatment), and total number of days hospitalized during and after an intervention. Measures of healthcare utilization that will be assessed include hospitalization events (total number of times hospitalized and cumulative days hospitalized), and the proportion of patients receiving a subsequent intervention for recurrent or persistent dysphagia. Hospitalization is defined as admittance to the inpatient setting of a hospital (medical or surgical ward or intensive care unit) for a period of ≥24 h per participant report.

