## Methods

### Study objectives

The goals of the TOEC-Eastern Africa study are:To describe the treatment patterns for ESCC at referral hospitals in Eastern Africa.To investigate the outcomes of different ESCC treatments in Eastern Africa, specifically overall survival, QOL, and safety, with a particular focus on palliative interventions including chemotherapy, radiotherapy with or without chemotherapy, esophageal stenting with SEMS, and supportive care.To examine process measures related to the delivery of ESCC treatment at referral hospitals in Eastern Africa, including time from presentation to initiation of treatment, total time to deliver an intervention, and total number of days hospitalized during and after ESCC treatment.To assess utilization of healthcare resources by ESCC treatment approach, as measured by hospitalization events (total number of times hospitalized and cumulative days hospitalized) and need for subsequent intervention for recurrent or persistent dysphagia.

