**Fig. 1 Fig1:**
[figure not shown]
Map of African Esophageal Cancer Consortium (AfrECC) study sites. “Map of African Esophageal Cancer Consortium (AfrECC) sites” published by Van Loon et al. The African Esophageal Cancer Consortium: A Call to Action. J Glob Oncol. 2018 Sep;4:1-9. Licensed under Creative Commons Attribution 4.0. Participant sites modified from original. License: https://creativecommons.org/licenses/by/4.0/

**Table 1 Tab1:** Characteristics of study sites in Eastern Africa

Site	Tenwek Hospital	Ocean Road Cancer Institute (ORCI)	Muhimbili National Hospital (MNH)	Kamuzu Central Hospital (KCH)	Moi Teaching and Referral Hospital (MTRH)	Kilimanjaro Christian Medical Centre (KCMC)
**Location**	Bomet, Kenya	Dar es Salaam, Tanzania	Dar es Salaam, Tanzania	Lilongwe, Malawi	Eldoret, Kenya	Moshi, Kilimanjaro
**Setting**	Rural	Urban	Urban (two campuses, Upanga and Mloganzila)	Urban	Urban	Urban
**Type of Hospital**	Faith-based hospital	National cancer (specialized) referral hospital	National referral hospital	National referral hospital	National referral hospital	Zonal referral hospital
**Recruitment start date**	February 2019	May 2019	November 2019	June 2021	November 2021	November 2021
**Recruitment end date**^**a**^	December 2022	December 2022	December 2022	December 2022	December 2022	December 2022
**Estimated annual new diagnoses of EC**	250	150	167	300	325	90
**Forecasted annual recruitment**	220	130	150	160	275	80
**Forecasted enrollment (total)**	862	476	472	253	320	93
**Duration of enrollment**	47 months	44 months	38 months	19 months	14 months	14 months

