**Diagnostic modalities available**						
Endoscopy	Yes	No	Yes	Yes	Yes	Yes
Pathology	Referred to outside facility	Yes	Yes	Yes	Yes	Yes
X-ray / ultrasound	Yes	Yes	Yes	Yes	Yes	Yes
CT scan	Yes	Yes	Yes	Yes	Yes	Yes
PET scan	No	No	No	No	No	No
EUS	No	No	No	No	No	Mo

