**Treatment modalities available**						
Chemotherapy	Yes	Yes	Yes^a^	Yes	Yes	Yes
Radiation						
Brachytherapy (for EC)	No	No	No	No	No	No
EBRT	No	Yes	No	Planned 2022	Yes	Referred to ORCI
Esophageal stents	Yes	No	Yes	Yes	Yes	Yes
Esophagectomy	Yes	No	Yes	No	Yes	No

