**Supportive care**						
Availability of TPN	Yes	Yes	Yes	Yes	Yes	Yes
Capacity for gastrostomy tubes	Yes	No	Yes	Yes	Yes	Yes
Intensive care unit	Yes	No	Yes	Yes	Yes	Yes
Palliative care team	Yes	Yes	No	Yes	Yes	Yes

Updated May 2021

*CT* Computed tomography, *EC* Esophageal cancer, *EBRT* External beam radiotherapy, *EUS* Endoscopic ultrasound, *PET* Positron emission tomography, *TPN* Total parental nutrition

^a^Chemotherapy is offered at MNH; most EC patients, however, are referred to ORCI for chemotherapy

In Tanzania, MNH is a public teaching hospital and national referral hospital affiliated with Muhimbili University of Health and Allied Sciences (MUHAS). MNH hosts 1500 beds, admitting 1000 to 1200 inpatients per week and providing care to more than 1000 outpatients per day. Following diagnosis, many of the cancer cases warranting chemotherapy and/or radiation therapy are referred to ORCI, the national cancer referral center in Tanzania, which hosts 273 beds. Muhimbili Academic Medical Center (MAMC) is a recently established public hospital affiliated with MNH. MAMC is located on the Mloganzila campus approximately 30 km from ORCI and MNH. Endoscopy services are available at both MNH and MAMC. KCMC is a public teaching hospital and zonal referral hospital located in Moshi, Tanzania. KCMC hosts 630 inpatient beds and sees an estimated 500-800 outpatients per day. It serves as the teaching hospital for the Kilimanjaro Christian Medical University College and hosts the Kilimanjaro Clinical Research Institute (KCRI), an affiliated research institution.

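### The re-intervention measure is tested as need but defined as receipt, and on-site access to re-treatment differs by site and is partly tied to radiotherapy

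*Protocol article*

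**What the plan says.** Three places in the protocol article describe this measure.

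- **Study objectives, fourth goal** (use of healthcare resources): "need for subsequent intervention for recurrent or persistent dysphagia".
- **Exploratory endpoints**, among the measures of healthcare utilisation: "the proportion of patients receiving a subsequent intervention for recurrent or persistent dysphagia". This is the only operational definition.
- **Statistical methods**: "Chi-squared test will be used to compare the need for subsequent intervention for recurrent or persistent dysphagia by treatment approach". No covariate or stratification is named for this test. The section adds that every analysis is done overall and repeated within each site.

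Table 1 gives the services at each site, in the order Tenwek, ORCI, MNH, KCH, MTRH, KCMC:

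- "Endoscopy Yes No Yes Yes Yes Yes"
- "Esophageal stents Yes No Yes Yes Yes Yes"
- "Capacity for gastrostomy tubes Yes No Yes Yes Yes Yes"
- "EBRT No Yes No Planned 2022 Yes Referred to ORCI"

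ORCI is the only site with a No on any of the first three rows. External beam radiotherapy is marked Yes only at ORCI and MTRH.

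**The concern.** Need and receipt are different variables. A patient with recurrent dysphagia who gets no further procedure is an event under the wording of the objective and the test, and a non-event under the endpoint definition.

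Receipt depends on what is available as well as on symptoms. Availability on site varies, and it varies partly with treatment: a large share of irradiated patients is likely to come from the one site that has no endoscopy, stenting or gastrostomy, while patients stented on site are by definition at sites that stent. A chi-squared test by treatment cannot separate a lower rate of recurrence from a lower chance of being re-treated.

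If the result is reported as need, a reader will probably set it against the trade-off described in the Discussion, where stents may fail over time and radiation may give more lasting control. A gap in access could then be read as a treatment effect.

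**Working it through.** **Step 1: is there a figure in the plan to reproduce?** No. The article states no re-intervention rate, no access rate and no power for this measure. What follows is illustrative.

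**Step 2: group sizes (Sample size section).** Stenting 1102; radiotherapy 464 + chemoradiation 212 = 676. The six forecast treatment groups sum to 1102 + 145 + 464 + 212 + 450 + 103 = 2476. The site forecasts in Table 1, "862 476 472 253 320 93", also sum to 2476.

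**Step 3: what share of radiotherapy patients could be at ORCI?**

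- Ceiling: 476/676 = 70%. This needs every ORCI patient to be irradiated, which is unlikely because ORCI also gives chemotherapy.
- If all 320 MTRH patients were irradiated and the rest were enrolled at ORCI: (676 − 320)/676 = 356/676 = 53%.
- The actual share is not given. I use 30%, 50% and 70%.

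**Step 4: illustrative model.** Assumptions, none of them from the documents: true need is 30% in both groups; everyone in need is re-treated, except that at ORCI only a fraction *a* is. Then

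receipt after stenting = 0.30

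receipt after radiotherapy = 0.30 × [1 − share × (1 − *a*)]

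Example with share 50% and *a* = 50%: 0.30 × (1 − 0.5 × 0.5) = 0.225. The pooled proportion is (1102 × 0.30 + 676 × 0.225)/1778 = 0.2715. The standard error is √[0.2715 × 0.7285 × (1/1102 + 1/676)] = 0.0217, so z = 0.075/0.0217 = 3.45.

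| Share at ORCI | *a* = 0% | *a* = 50% | *a* = 80% | *a* = 100% |
|---|---|---|---|---|
| 30% | 21.0%, z 4.17 | 25.5%, z 2.05 | 28.2%, z 0.81 | 30%, z 0 |
| 50% | 15.0%, z 7.16 | 22.5%, z 3.45 | 27.0%, z 1.36 | 30%, z 0 |
| 70% | 9.0%, z 10.37 | 19.5%, z 4.90 | 25.8%, z 1.91 | 30%, z 0 |

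Each cell gives the receipt rate after radiotherapy, to be compared with 30% after stenting, and the pooled z that corresponds to the planned chi-squared test. The critical value is 1.96 at 0.05, or 2.39 if 0.05 is divided by three comparisons.

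The probability that the test at 0.05 shows a spurious difference, for *a* = 0%, 50% and 80%, is 0.99, 0.53 and 0.12 at a 30% share; 1.00, 0.94 and 0.27 at 50%; and 1.00, 1.00 and 0.48 at 70%. At *a* = 100% it is the nominal level.

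**Step 5: does the within-site repeat solve it?** Not at ORCI, which places no stents and so has no on-site stent comparator. At MTRH (forecast 320), which has radiotherapy, stents, endoscopy and gastrostomy, it does give a comparison under equal on-site access.

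**The case against.** The strongest reply is that this is a utilisation measure. The objective concerns use of resources, the endpoint is listed under utilisation and is exploratory, and receipt is a valid measure of utilisation. On that view, need is only loose wording. This stands as far as the endpoint definition goes. It does not justify announcing a receipt rate as need.

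Durability also has its own secondary endpoints, duration of dysphagia relief and dysphagia-adjusted survival. Both are based on scores and compared with log-rank tests and adjusted Cox models. That stands too: the main durability question does not depend on this measure.

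A reader might go further and infer that radiotherapy will look more durable because re-treatment is out of reach at ORCI. The documents do not support that:

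- MNH is in the same city, is linked to ORCI by referral and offers all three services. Nothing says that ORCI patients cannot be re-treated there, or that treatment elsewhere goes uncounted.
- MTRH combines radiotherapy with all three services. KCMC refers for radiotherapy to ORCI but has the three services itself.
- A subsequent intervention is not limited to endoscopic procedures, and ORCI offers chemotherapy and radiotherapy. Tenwek and MNH, conversely, have no radiotherapy on site. Even the direction of the net effect is therefore likely rather than certain.

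**Conclusion.** The mismatch is real: the objective and the test speak of need, while the definition counts receipt. Treatment is partly confounded with on-site access to re-treatment, and the planned overall test takes no account of this.

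The size is unknown. It depends on the share of radiotherapy patients at ORCI (70% at most on the forecasts) and on how many of those in need are re-treated, for which the documents give nothing. Under the stated assumptions, a spurious difference is near certain if ORCI patients have no route to re-treatment. It is modest if 80% of those in need are re-treated, with z below 1.96 at all three shares, and it vanishes when access is equal.

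Because the endpoint is exploratory and durability is measured separately, this is a point about labelling and analysis of one measure. It does not threaten the main comparisons.

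**What to change.** 1. In the fourth objective and in Statistical methods, call the measure receipt of a subsequent intervention, as a utilisation outcome that matches the endpoint definition.
2. Compare it with stratification by site, or by whether stenting is available on site. State that it will not be interpreted as need or durability.
3. If need is to be compared, define it from the dysphagia scores, for example as a return to the pre-treatment score or worse at a scheduled call. Report it beside receipt and do not merge the two: in a composite, a patient with partial relapse would still be an event only if re-treated, which brings access back in.
4. Label any statement of the likely bias as illustrative, and show it over a range of ORCI shares and access rates.

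The cost is a few changes of wording and one stratified test, using site and dysphagia data already collected. There are three downsides. Score-based need is seen only at scheduled calls. It overlaps with duration of dysphagia relief. A stratified comparison of stenting with radiotherapy draws little or nothing from ORCI, so it will be less precise and will rest largely on sites such as MTRH.
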